#### Breathlessness

The following questionnaires will be used to assess different aspects of breathlessness and to help select appropriate patient-reported outcome measures for the future trial:

Dyspnoea-12 is a brief 12 item, self-complete, questionnaire which has been found to reliably measure breathlessness in a variety of diseases.^23^ Dyspnoea has both sensory and afferent components and this tool was developed to ensure both aspects could be measured.The Multidimensional Dyspnoea Profile is a self-complete questionnaire for breathlessness divided into an immediate perception domain and an emotional response domain.^31^ This questionnaire shows responsiveness to change in an acute and routine care setting for patients with breathlessness.^31^The Baseline Dyspnoea Index and Transition Dyspnoea Index are short interviewer led questionnaires involving open questions about how their breathlessness affects everyday life.^32^ This is measured over time in respect to what tasks a patient can manage and how much effort is required to complete a task.The MRC Dyspnoea Grade 5-point scale is patient completed and requires participants to indicate to what extent their breathlessness limits their function by working down the statements which increase in severity regarding functional limitation.^33^

#### Anxiety and depression

Participants will also complete the Hospital Anxiety and Depression scale which is a simple self-completed questionnaire with 14 questions relating to either anxiety or depression^34^

#### Activation measure

The Patient Activation Measure is a self-completed questionnaire which assesses patients’ knowledge, skills and confidence to manage their own health.^35^

#### Physical activity

Daily physical activity and stationary time will be assessed for 7 days using the GT3x ActiGraph device that is worn around the waist,^36^ and the wrist worn GENEActiv device.^37^ Sedentary time, daily step count and time spent in moderate and vigorous physical activity will be recorded. The activity monitors will be fitted at visits 1 and 2 and will be programmed to begin collecting data at midnight. Data will then be collected for 7 days thereafter. To maximise the use of the data for comparison with other disease data sets we will use both devices as long as patients are willing. If participants can only use one device we will request that this is the wrist worn GENEActiv.

#### Exercise capacity

This will be assessed using the Incremental Shuttle Walk Test (ISWT).^38^ This walking test requires the patient to walk between two cones nine metres apart in time to a set of auditory beeps. Initially, the walking speed is very slow, but each minute the required walking speed progressively increases. The patient will walk for as long as they can until they are either too breathless or can no longer keep up with the beeps at which time the test ends. It is reported as the distance walked. The ISWT is found to be valid, reliable and responsive in patients with chronic heart and respiratory disease.^39–41^

Heart rate, oxygen saturations, blood pressure and BORG breathlessness score will be recorded before and after completion of the walk tests. A practice walk test will be performed as per the guidelines for this exercise test.

#### Frailty

Fried’s frailty definition will be recorded, which is based on patient reported weight loss and exhaustion along with measured slowness (gait speed), weakness (hand grip) and physical activity.^42^ This has been shown to provide a standardised definition of frailty with predictive validity in the community dwelling older population.^43^ The Rockwood Frailty Scale will also be recorded. This is completed by the researcher in response to medical history and outcome measures taken during the visit and has also been demonstrated as a valid and reliable way of documenting frailty.^44^

Participants will also complete the Timed Up and Go test where the patient starts in a seated position, stands and walks 3 metres, then turns around and returns to the seated position.^45^ The patient is timed how long this process takes.

The Short Physical Performance Battery^46^ which includes the 4-Metre Gait Speed test and the Sit-to-Stand test and assessing balance with the patient standing in different positions (side by side stand, semi tandem stand, tandem stand) will be completed, along with handgrip and quadriceps strength.

#### Health economic modelling

The feasibility study is structured to support the future RCT which will estimate the lifetime incremental cost per QALY gained. The objectives are to identify: the main NHS and prescribed specialist services cost components; the resource use and unit cost data required for each of these components; potential sources of HRQoL data suitable for estimating QALYs in this patient group; potential sources that could be used to estimate residual life expectancy and other long-term outcomes among patients.

#### Semi-structured interviews

Audio-recorded interviews will be conducted privately face-to-face or via telephone between the participant and an interviewer, following informed consent. Interviews will take place with patients and GPs until data saturation is perceived. The interviews are anticipated to be between 30 min and 1 hour duration and will be professionally transcribed verbatim, with identifiable information removed. The transcription will be performed by an external company and a confidentiality agreement will be in place. Interview prompts will be devised based on relevant literature, experience of the team and consultation with patient representatives.

Patients consented for the feasibility trial who are willing and able, and healthcare staff from the participating practices, will be interviewed.

The interviews will explore patients’ experience of breathlessness, taking part in the trial and their related healthcare. Patients will also be asked about the acceptability of the research visits and outcome measures performed and about their understanding of the trial. Interviews with healthcare staff will seek to understand what is usual care and any influence that taking part in the trial has on usual care. The clinician interviews will include questions about what a diagnostic pathway should or could look like from the perspective of the health professionals. They will also explore any barriers to screening patients for eligibility, challenges in implementing the pathway or perceived benefits of the intervention. The patient participant and clinician interview guides can be viewed in the online supplemental.

#### Data management

Paper based anonymised study records will be stored in locked filing cabinets within a locked office at Glenfield Hospital. Electronic records will be stored on a restricted access, secure University of Leicester and University Hospitals of Leicester NHS Trust computer system, maintained by the Trust. Audio recordings will be done using an encrypted Dictaphone. The recordings will be uploaded to secure files on University of Leicester and University Hospitals of Leicester computers then deleted from the Dictaphone. Access to the files will be restricted and password protected.

#### Data analysis

Data analysis will be performed in an exploratory fashion. Descriptive statistics, number and percentage for categorical data and mean and SD or median and IQR for non-normally distributed continuous data will be present for all demographics, baseline characteristics and questionnaire scores. Normality of the baseline characteristics will be determined using the Kolmogorov-Smirnov test or Shapiro-Wilk test depending on final recruitment numbers.

SPSS V.26 will be used for statistical analysis. GraphPad software will be used for any figures. Data analysis will be performed on the complete data set using all participants.

Secondary outcomes for both groups will be described as mean (SD) and median (IQR) for normally or non-normally distributed data, respectively. The time to diagnosis will be analysed using survival analyses based on Cox proportional hazards survival modelling. The proportion of patients with valid diagnosis at 3 months and 1 year will be described and compared using χ^2^ tests.

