### Trial design and registration

This is a 1-year feasibility cluster RCT recruiting from primary care. Ten GP practices from East and West Leicestershire and Leicester City clinical commissioning groups (CCG) will be cluster randomised to a structured diagnostic pathway or usual care. The intervention practices will follow a structured diagnostic pathway to include early investigations. Usual care will continue without any intervention.

The University of Leicester will act as study sponsor and the trial has been registered on the ISRCTN website.

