#### Eligibility criteria for GP practices

GP practices will be approached to take part in this study if they serve a patient population over 10 000. Practices that are research active, as identified by the local Clinical Research Network research scheme, will be approached. The practices will be visited by the study team to discuss taking part in the study and engage with the practice teams.

The GP practices will be randomised 1:1 and stratified by CCG using Statarand,^25^ a Stata randomisation module (Boston College Department of Economics).

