### Outcomes

As this is a feasibility trial, a formal sample size/power calculation is not required. Recruitment itself is one of the main measures of feasibility. The feasibility measures are outlined in box 1 and the secondary outcome measures in table 1. Recruitment rate will be recorded as a proportion of participants consented compared with the number of participants identified as eligible by the GP practices.

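### Practices are randomised, but the proportions of patients diagnosed are compared with χ² tests that assume independent patients; the Cox analysis states no allowance for practice

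*Protocol article*

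**What the plan says.** On design, the section Trial design and registration of the protocol article states: "Ten GP practices from East and West Leicestershire and Leicester City clinical commissioning groups (CCG) will be cluster randomised". The section Eligibility criteria for GP practices adds: "The GP practices will be randomised 1:1 and stratified by CCG using Statarand".

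On analysis, the Data analysis section names two between-arm methods, both for diagnosis outcomes. The first is for time to diagnosis: "The time to diagnosis will be analysed using survival analyses based on Cox proportional hazards survival modelling". The second is for the proportions: "The proportion of patients with valid diagnosis at 3 months and 1 year will be described and compared using" χ² tests. The same section says "Data analysis will be performed in an exploratory fashion" and "Data analysis will be performed on the complete data set using all participants". Other secondary outcomes are only described by group.

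The article nowhere mentions practice or CCG as a term in the analysis, an ICC, a frailty or random effect, a cluster-robust variance, or practice-level summaries.

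**The concern.** The χ² test is valid when patients are independent of one another. Here the practice is allocated, and the practice delivers the intervention: template prompts, a laminated pathway document and workstation cards in one arm, the practice's own habits in the other. How fast a patient is diagnosed is therefore likely to depend partly on the practice. With positive within-practice correlation, the variance of the arm difference exceeds what the χ² test assumes, and its p-value is too small. A normal reference based on patient numbers also ignores that only ten units were randomised.

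At stake is what the feasibility study passes on. The specific aims in the Introduction include choosing the main trial's primary outcome, learning what difference is realistic, and working out the number of practices and cluster sizes. A chance difference between two sets of five practices could be reported as a signal. An analysis that ignores practice also yields no ICC, which the cluster-size calculation needs.

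**Working it through.** The article gives no sample size, significance level or ICC, so there is no figure of its own to reproduce. The check shows the size of the error over a range.

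**From the document:** 10 practices, allocated 1:1 (taken as 5 v 5), stratified by three CCGs; χ² tests on patients.

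**Assumed:** m = 10 or 20 patients per practice, equal across practices; ICC 0.01 to 0.10; 50% diagnosed; two-sided 5% level; no true effect.

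**Step 1, formula.** Design effect DE = 1 + (m − 1) × ICC. The true standard error is √DE times the naive one. Approximate true type I error = 2 × (1 − Φ(1.96/√DE)).

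Example, m = 10 and ICC 0.05: DE = 1 + 9 × 0.05 = 1.45 and √1.45 = 1.204. The naive standard error is 1/1.204 = 0.83 of the true one, so 17% too small. Type I error = 2 × (1 − Φ(1.96/1.204)) = 10.4%. The 100 patients carry the information of 100/1.45 = 69.

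**Step 2, simulation.** Beta-binomial data, 5 v 5 practices. The uncorrected χ² test is set beside the continuity-corrected version, because the article does not say which is meant. The setting with no clustering separates the effect of clustering from small-sample discreteness.

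| m | ICC | DE | Formula | Uncorrected χ² | Corrected χ² |
|---|---|---|---|---|---|
| 10 | 0 | 1.00 | 5.0% | 5.7% | – |
| 10 | 0.01 | 1.09 | 6.0% | 6.9% | 4.4% |
| 10 | 0.05 | 1.45 | 10.4% | 11.5% | about 8% |
| 10 | 0.10 | 1.90 | 15.5% | 17.1% | about 13% |
| 20 | 0 | 1.00 | 5.0% | 5.6% | – |
| 20 | 0.01 | 1.19 | 7.2% | 8.0% | about 6% |
| 20 | 0.05 | 1.95 | 16.0% | 17.4% | about 14% |
| 20 | 0.10 | 2.90 | 25.0% | 26.6% | about 23% |

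**Step 3, practice-level alternative.** A two-sample t test on the ten practice proportions has 10 − 2 = 8 df (critical value 2.306 instead of 1.96). It held about 5% in the same settings. Adjusting for three CCGs uses two more parameters, leaving 10 − 2 − 2 = 6 df.

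**Step 4, time to diagnosis.** This step applies only if the Cox model is fitted without allowance for practice. The unadjusted log-rank test (the Cox score test) was simulated with gamma shared frailty and about 50% diagnosed by 12 months. At frailty variance 0, 0.05, 0.1 and 0.2 the type I error was 5.2%, 7.3%, 10.7% and 14.9% at m = 10, and 4.6%, 10.6%, 14.8% and 24.0% at m = 20.

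**The case against.** The strongest reply has four parts.

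**The article condenses a fuller document, and the Cox sentence names only a family of models.** This stands. A shared-frailty or cluster-robust version would fit the wording. A reader might infer that an ordinary, unadjusted Cox model is planned; the text does not say so. The reply does not reach the χ² tests. There the article names a specific test that requires independence, so an analysis plan that follows it carries the error and one that corrects it departs from the article.

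**The comparisons are secondary and exploratory.** This stands as to weight. A reader might infer that these tests decide whether the pathway works, or that the main result is at risk. The article ties no significance rule or progression criterion to them, and recruitment rate is untouched. The point estimates are not shown to be biased, and the article promises no confidence intervals for these comparisons. But an exploratory label limits interpretation; it does not make a variance correct.

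**Part of the excess over 5% is not clustering.** This stands at the low end. Without clustering the uncorrected test already runs at about 5.7% (m = 10), and with a continuity correction and an ICC of 0.01 there is no inflation above 5% at m = 10. At larger ICCs or m = 20 the excess is clearly due to clustering.

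**Testing without a power calculation is no contradiction.** The Outcomes section says "a formal sample size/power calculation is not required" because this is a feasibility trial. Exploratory tests need no power calculation, so nothing is wrong there.

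**Conclusion.** The point holds for the χ² tests: they ignore the unit of randomisation and give p-values that are too small whenever the ICC is above zero. Across ICC 0.01 to 0.10, the true type I error of a nominal 5% test is about 7–17% at 10 patients per practice and 8–27% at 20 for the uncorrected test, or about 4–13% and 6–23% with a continuity correction. Cluster sizes, ICC and the 50% diagnosed are assumptions. With no within-practice correlation the error is close to nominal.

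For the Cox analysis the finding is narrower: allowance for practice is unstated and should be stated.

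This is a should-fix. It leaves the primary outcome alone but affects comparisons that inform the main trial's outcome and realistic difference.

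**What to change.** In the Data analysis section:

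- Replace the χ² tests with a comparison of practice-level proportions diagnosed: the arm difference with a 95% CI from a t distribution on 8 df, or 6 df when adjusted for the three CCGs.
- State that the Cox model accounts for practice, by shared frailty or by a cluster-robust variance with a small-sample correction. With ten clusters an uncorrected robust variance would itself be too small.
- Treat CCG the same way in both analyses.
- Report estimates with intervals, and the ICC, instead of significance claims.

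Cost: wider intervals, and a small protocol amendment, which the Protocol amendments section routes through the ethics committee with sponsor agreement. The article names SPSS V.26 for analysis, and the Cox part may need other software. Recruitment, visits and data collection do not change.

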Our overarching hypothesis is that a symptom-based approach for diagnosis in primary care for patients with chronic breathlessness will lead to earlier diagnosis, earlier treatment and improved outcomes such as health-related quality of life (HRQoL). However, it is also important to consider the implications of over investigating and ‘over-diagnosis’ in patients and find the balance between clinical and cost-effectiveness for a diagnostic pathway.^22^ A large and potentially expensive multicentre cluster randomised controlled trial (RCT) would be necessary to understand the clinical and cost-effectiveness of a structured diagnostic pathway for chronic breathlessness. The scope of this study is to assess the feasibility of such a trial and help inform the design.

For this feasibility study the specific aims are:

To assess feasibility by recruitment and retention rate of patients in the trial to enable calculation of the number of GP practices, cluster sizes and duration of the ultimate RCT (box 1).To better understand ‘usual care’ through prospective observation and qualitative analysis, and to understand any influence of the trial design on usual care.To determine the proposed primary outcome measure for the future trial and to increase understanding of what is an important and realistic difference while exploring potential of other outcome measures (table 1).Identify sources of data and how best to collect these in order to plan the economic evaluation that would accompany a full trial.

Box 1Feasibility measuresFeasibility measuresNumber of patients recruited per week per general practitioner (GP) practice population size.Number of participating GP practices verses the number approached.Time for GPs to screen for eligibility.Number of eligible patients who agree to be approached by the research team verses total number of eligible patients.Number and timing of investigations in the diagnostic pathway completed.Acceptability of the research visit to the participants.Data collected from interviews regarding participant experience of the trial.Data collected from interviews regarding GP experience of participating in the trial and influence on their practice.

**Table 1 T1:** Secondary outcome measures

Secondary outcome measures	Measurement tool
Proportion of diagnoses in usual care and intervention within 1 year of presentation	Review of healthcare records for all participants

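### The proportions diagnosed are compared by ordinary χ² tests, which ignore randomisation by practice and give no interval for the between-arm difference

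*Protocol article*

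**What the plan says.** The article describes a feasibility trial in which ten GP practices are randomised 1:1, stratified by clinical commissioning group (Trial design and registration; Eligibility criteria for GP practices). Recruitment rate is the primary outcome (Abstract). Outcomes states: "As this is a feasibility trial, a formal sample size/power calculation is not required".

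Data analysis opens with "Data analysis will be performed in an exploratory fashion" and promises numbers and percentages for categorical data. For the diagnosis outcomes it goes further:

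- Time to diagnosis: "The time to diagnosis will be analysed using survival analyses based on Cox proportional hazards survival modelling".
- Proportion diagnosed: "The proportion of patients with valid diagnosis at 3 months and 1 year will be described and compared using" χ² tests.

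No between-arm difference, ratio or confidence interval is named, and neither method is said to allow for practice. Part of the third aim in the Introduction is "to increase understanding of what is an important and realistic difference while exploring potential of other outcome measures".

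**The concern.** The χ² test is the only between-arm significance test that the article names, and it is applied at two time points. It has two weaknesses here.

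- **Unit of analysis.** Patients of one practice share clinicians, access to tests and an allocated arm. If their outcomes are positively correlated, a test that counts them as independent understates the standard error and rejects too often. An interval built on the same footing would be too narrow.
- **Type of output.** Planning a larger trial calls for the range of differences still compatible with the data. A χ² statistic does not give that range, and the described percentages give a point difference without its uncertainty.

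At stake is how the diagnosis results are read when the future trial is designed. A difference could look firmer than ten practices can support.

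**Working it through.** The article states no sample size, power, alpha, diagnosis rate or ICC, so there is no figure of its own to reproduce. What follows is an illustration.

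**Inputs from the article:** 10 practices, 1:1, so about 5 per arm and 10 − 2 = 8 degrees of freedom for a comparison of practice-level results.

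**Assumed inputs:** total N of 50, 100 or 200 patients, equal practice sizes m = N/10, 50% diagnosed, ICC 0.05 (range 0.01 to 0.10), two-sided 5% level.

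**Formulas**

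- Design effect: DE = 1 + (m − 1) × ICC
- Standard error of the difference if patients were independent: SE₀ = √(2 × 0.25 / (N/2))
- Standard error allowing for practice: SE = SE₀ × √DE
- 95% half-width: 1.96 × SE₀ if independent; 2.306 × SE allowing for practice (t, 8 df)
- Type I error of the ordinary χ² test: 2 × [1 − Φ(1.96/√DE)]

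**Worked case, N = 100.** m = 10 and DE = 1 + 9 × 0.05 = 1.45. SE₀ = √(0.5/50) = 0.100 and SE = 0.100 × √1.45 = 0.120. The half-widths are 1.96 × 0.100 = 0.196 and 2.306 × 0.120 = 0.278. The type I error is 2 × [1 − Φ(1.96/1.204)] = 0.104.

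| N | DE | SE₀ | SE | Half-width, independent | Half-width, by practice | χ² type I error |
|---|---|---|---|---|---|---|
| 50 | 1.20 | 0.141 | 0.155 | ±28 points | ±36 points | 7.4% |
| 100 | 1.45 | 0.100 | 0.120 | ±20 points | ±28 points | 10.4% |
| 200 | 1.95 | 0.071 | 0.099 | ±14 points | ±23 points | 16.0% |

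**Sensitivity to the ICC.** Over N = 50 to 200 and ICC 0.01 to 0.10, the practice-based half-width runs from ±18 points (N = 200, ICC 0.01) to ±39 points (N = 50, ICC 0.10). The χ² type I error runs from 5.5% (N = 50, ICC 0.01) to 25% (N = 200, ICC 0.10). More patients per practice narrow the interval but worsen the error of the unadjusted test.

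**Cox model.** With an assumed 50 diagnoses split evenly between arms, the 95% interval is the hazard ratio divided or multiplied by exp(1.96 × 2/√50) = 1.74. This is before any allowance for practice, which would widen it when outcomes within practices are positively correlated.

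**Limits.** Unequal practice sizes would tend to widen these intervals further. The 8 df ignore the stratification; an analysis that adjusts for commissioning group has fewer.

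**The case against.** The other side has a good case on several points.

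- **A reader might infer that the only output is a p-value.** The text does not support this. The proportions are described as well as compared, so the size of the difference can be read off. Only its uncertainty is unnamed.
- **A reader might infer that both diagnosis outcomes are put to significance tests.** The Cox model estimates a hazard ratio, and no test or threshold is named for it. What it lacks is a stated allowance for practice.
- **A reader might see a contradiction with the absence of a power calculation.** There is none. A feasibility trial may go without one and still make an exploratory comparison.
- **A reader might conclude that ten practices cannot settle whether the pathway speeds diagnosis.** That depends on the true difference, which is unknown. At ICC 0.05 and N = 50, 100 and 200, power is 14%, 20% and 27% for a true 15 points, but 40%, 59% and 76% for 30 points.
- **A reader might fear that the observed difference will become the future target difference.** The article never says so. Aim 3 also covers the choice among many outcome measures, and it is not tied to the χ² result.

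It can also be said that intervals are often left to a fuller protocol or analysis plan, neither of which is shown. That excuses silence on detail. It does not excuse the method that is named: the article chooses a patient-level test for a practice-randomised comparison. The exploratory label tempers how the result is read but does not correct the standard error.

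**Conclusion.** The point holds as a matter of method for a secondary, exploratory analysis. The named χ² tests do not match the unit of randomisation, and the described proportions come without a valid interval for their difference. With 50% diagnosed and ICC 0.05, the size is a type I error of about 7% to 16% and an interval of about ±36 to ±23 points for 50 to 200 patients. Patient number, diagnosis rate and ICC are all assumed. At ICC 0.01 the type I error is only 5.5% to 7.2%, so the error-rate part could be small, but even then the interval is at best ±18 points within this range.

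Recruitment rate and the other feasibility measures are not touched. The documents do not support a ban on p-values or added restrictions on aim 3.

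**What to change.** In Data analysis:

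1. Replace the χ² tests, as the main result, by the difference in proportion diagnosed at 3 months and at 1 year, each with a 95% interval computed from the practice-level proportions (t with 8 df).
2. Report the Cox hazard ratio with a 95% interval that allows for clustering by practice, using a method suited to ten clusters.
3. Label any p-value exploratory.

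The cost is a few lines of text, a little more analysis work and wider intervals. No new data are needed beyond the practice identifier.
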